### Safety evaluation

In general, toxicities that occur when irradiating the whole brain in patients with brain tumors or brain metastases include headache, nausea, vomiting, fatigue, anorexia, scalp irritation/discoloration, hair loss, and abrupt cognitive decline. However, since the radiation dose that will be used in this study is much lower than used in patients with brain tumor (up to 5%), the aforementioned side effects are expected to be rare. Potential toxicities related to LDRT to the whole brain will be evaluated based on the Common Terminology Criteria for Adverse Events v6.0.

### Sample size calculation

This trial is intended to further evaluate the treatment effect of LDRT on AD, and it is difficult to calculate the appropriate effect size for the treatment and control groups. Therefore, the purpose of this study is exploratory, in the form of a pilot study to compare efficacy. Bonferroni correction will be performed, and a comparative, parallel, three-arm design will be adopted with 80% power and a 2-sided alpha of 0.05. Finally, 20 people per group, for a total of 60 people, is calculated as the number of samples considering the dropout rate.

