### Baseline and randomization (Visit 2)

Eligible patients will be assigned to three treatment groups (two experimental groups and one control group) by stratified block randomization using a random number table. The researcher will obtain consent and assign the screening number to each participant in order. After confirming eligibility, the participants will finally be enrolled, and a treatment group will be assigned based on a pre-generated random assignment table. Randomization will be performed on three treatment groups at a 1:1:1 ratio: 24 cGy/6 fractions of LDRT, 300 cGy/6 fractions of LDRT, or sham RT. After allocation, patients will undergo CT simulation of the whole brain using personalized immobilization devices. Treatment planning will be performed using three-dimensional conformal RT.

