### Outcome measures (primary and secondary endpoints)

The primary endpoint is the score change of ADAS-K (range 0–70, higher scores indicate a worse outcome) 6 months after baseline and the number of adverse events 6 months after baseline determined by the Radiation Therapy Oncology Group toxicity grading system. The amount of change will be evaluated as a valid response if it shows an improvement of≥5% from the baseline score.

The secondary endpoints include the score change of K-MMSE-2 (range 0–30, higher scores mean a better outcome), CDR (range 0–3, higher scores mean a worse outcome), CGI-NPI (range 0–144, higher scores mean a worse outcome), and K-iADL (range 10–33, higher scores mean a worse outcome) after 6, 12 months from baseline. Also, we will additionally assess the primary endpoint 12 months after baseline. Changes in the SUVR of amyloid PET scans in the frontal, parietal, lateral temporal lobe, anterior wedge, and posterior gyri will be evaluated. The evaluation of the valid response is the same as that of the primary endpoint.

Furthermore, the primary endpoint evaluation will be analyzed by three institutions, and an additional analysis will be conducted to determine whether there are any differences among institutions.

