To determine the daily dose for the experimental groups, we referenced an experimental paper on radiation dose-dependent hippocampus apoptosis in adult mice [24]. In this study, dose-response curves were linear-quadratic, with a significant relationship between the appearance of cell death and irradiation dose in the range of 0–2 Gy. Furthermore, in a recent review article on low dose ionizing radiation affecting the immune system, Lumniczky et al. divided daily doses into three groups based on the following ranges: low-doses (<100 mGy), intermediate-doses (100 mcGy to 1 Gy), and high-doses (>1 Gy). High-doses mainly have immunosuppressive and pro-inflammatory effects, while low-doses have sustained immunomodulatory and anti-inflammatory effects [25]. Based on these facts, we adopted two experimental daily doses less than 1 Gy. The determination of the irradiation dose in experimental group 1 was based on a case report by Cuttler et al. [9], which showed remarkable cognitive improvement through a total of 5 trials of approximately 40 mGy per brain CT scan. The dose in experimental group 2 was determined according to Yang et al. [6]. In this study, mice will be irradiated with a total dose of 300 cGy (5 fractions×60 cGy) to prevent the accumulation of Aβ plaques and alleviate cognitive decline. A daily dose of 200 cGy, which is currently used in other ongoing clinical trials, will not be used in this study because there was no therapeutic effect in the LDRT study at a daily dose of 180 cGy conducted by our research team as a pilot study (NCT04203121). A recent study by Rogers et al. showed promising results using a daily dose of 200 cGy, but it was a pilot study with only five patients, so the reliability of the daily dose cannot be determined [17]. To rule out a placebo effect, the control group will receive sham irradiation. Therefore, in this study, two experimental groups will be used: 4cGy per fraction (a total of 24 cGy/6 fractions) and 50 cGy per fraction (a total of 300 cGy/6 fractions) to verify the treatment effect compared with that in the control group (sham RT).

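### The plan fixes plain Bonferroni, although Holm's step-down over the two dose-versus-sham ADAS-K comparisons keeps the same 5% familywise error and never has less power

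*Protocol article*

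**What the plan says.** All references are to the protocol article.

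- **Sample size calculation.** "Bonferroni correction will be performed, and a comparative, parallel, three-arm design will be adopted with 80% power and a 2-sided alpha of 0.05". The same section says that "it is difficult to calculate the appropriate effect size for the treatment and control groups", calls the work exploratory ("the purpose of this study is exploratory, in the form of a pilot study to compare efficacy"), and ends with "Finally, 20 people per group, for a total of 60 people, is calculated as the number of samples considering the dropout rate". It gives no standardized difference, SD or dropout rate.
- **Baseline and randomization (Visit 2).** Allocation to the three arms is equal.
- **Outcome measures.** "The primary endpoint is the score change of ADAS-K" at 6 months. The same sentence adds "the number of adverse events 6 months after baseline". The Abstract names the ADAS-K change alone as primary.
- **Discussion, dose rationale.** The two dose arms are there "to verify the treatment effect compared with that in the control group (sham RT"), which makes two comparisons sharing one sham arm.
- **Statistical analysis.** Unpaired tests are named for baseline characteristics. For the change from baseline to 6 months, only paired tests within each group are named.

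**The concern.** The multiplicity method is a stated choice, not a detail left open. Bonferroni over two tests holds each at 0.025 whatever the other shows. Holm tests the smaller p-value at 0.025 and, if that succeeds, the larger at 0.05. It rejects everything that Bonferroni rejects and sometimes more. It also has the same strong familywise control and needs no added assumption about how the two tests depend on each other.

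The trial has 20 patients per arm and sets out to explore the appropriate dose. A verdict on both doses is therefore of interest, and that is the only place where the two methods differ. At stake is power for the second dose, at no cost in patients.

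The correction also needs something to act on. A paired test within one arm is not a comparison with sham.

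**Working it through.** **Step 1. The plan's own figure.** For two means with equal arms, the normal formula is n = 2(z₁₋α/₂ + z₀.₈)² / d², where d is the difference in SD units. With two tests α = 0.025, so z = 2.241 and z₀.₈ = 0.842, and n = 2 × 3.083² / d² = 19.0 / d².

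- d = 1.0, no dropout: 19.0, rounded up to 20.
- d = 1.1, 20% dropout: 19.0 / 1.21 = 15.7, rounded up to 16; 16 / 0.8 = 20.

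Both give the plan's 20 per group. Since d and dropout are not stated, the figure can be neither reproduced uniquely nor refuted. With 20 evaluable per arm, 80% power at 0.025 needs d of about 0.98 by the normal formula, or 1.01 by the t-test.

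**Step 2. Rules compared.** Let p₁ and p₂ be the two-sided p-values of the two dose-versus-sham t-tests.

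- Bonferroni: reject each if its p < 0.025.
- Holm: if min(p₁, p₂) < 0.025, reject that one, and reject the other if its p < 0.05.

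Both rules need min(p₁, p₂) < 0.025 for any rejection, so the chance of at least one win is identical. Holm differs only when one p is below 0.025 and the other lies between 0.025 and 0.05.

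**Step 3. Size.** Simulation with 200,000 trials per scenario, normal outcomes, one shared sham arm and two-sample t-tests. All values of d are assumed. The 17 per arm is 20 × 0.85, an assumed dropout of 15%. Each cell shows Bonferroni over two tests, then Holm.

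| d in the two dose arms | n per arm | Power per dose | Both doses | At least one |
|---|---|---|---|---|
| 1.0 and 1.0 | 20 | 79.4% → 84.3% | 67.9% → 77.7% | 90.9% → 90.9% |
| 0.8 and 0.8 | 20 | 58.0% → 63.8% | 41.7% → 53.3% | 74.3% → 74.3% |
| 0.5 and 0.5 | 20 | 23.8% → 26.9% | 11.2% → 17.3% | 36.4% → 36.4% |
| 1.0 and 1.0 | 17 | 71.2% → 76.8% | 57.1% → 68.4% | 85.3% → 85.3% |
| 1.0 and 0 | 20 | active dose 79.4% → 79.5% | – | 80.2% → 80.2% |

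**Step 4. Consistency check.** The two per-dose powers must sum to P(at least one) + P(both). For Holm at d = 1.0, n = 20: 90.86% + 77.70% = 168.56%, and 84.24% + 84.32% = 168.56%.

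**Step 5. Error.** With neither dose active, the familywise error is 4.6% for each method. With one dose active at d = 1.0, the chance of wrongly declaring the other rises from 2.5% to about 4.25%. Holm uses more of the allowance here, but stays within 5%.

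**The case against.** Bonferroni is valid. It controls the familywise error, it suits a study that calls itself an exploratory pilot, and it gives simultaneous intervals that always agree with the tests. All of that stands, so this is a matter of efficiency and not an error. But the plan itself invokes 80% power, a two-sided 5% level and a multiplicity correction. Having chosen familywise control, it loses no error control by taking the more powerful version.

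It is also fair to say that the gain is conditional. The 10-point gain for both doses needs 24 cGy and 300 cGy, a 12.5-fold difference, each to work by about one SD. If only one dose works, Holm is worth almost nothing.

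A reader might go further and infer that the per-test level is undefined, because the tests could number three (all pairs), or four or six once adverse events are counted, with a matching loss of power. The documents do not support that as a finding. How many tests share the 5% is detail that a condensed article may leave to the full protocol. No section states a four- or six-test family; the correction is tied to a three-arm comparison of efficacy. And if a larger family were meant, most of the gain would come from cutting it to two tests, which is not the same error control.

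Finally, the two-comparison reading rests on the Discussion's dose rationale, not on the analysis section. That is a reason to write the comparisons down.

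**Conclusion.** The point holds as a modest and cheap improvement. For the two dose-versus-sham comparisons of 6-month ADAS-K change, Holm is never less powerful than the stated Bonferroni at the same 5% familywise ceiling. That ordering depends on no assumed value.

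The size does depend on assumptions, since the article gives no effect size, SD or dropout rate. With both doses equally effective and 20 evaluable per arm, the gain is about 5 points per dose and 10 points for both at d = 1.0, and about 3 and 6 points at d = 0.5. It is zero for at least one win and about 0.2 points if only one dose works.

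A reader might also infer that settling the correction would make the 80% power claim interpretable. It would not, because the effect size and SD would still be missing.

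**What to change.** Replace the Bonferroni statement with wording to this effect: the two-sided familywise 5% covers two between-arm comparisons of ADAS-K change at 6 months, 24 cGy against sham and 300 cGy against sham. They are tested by Holm's procedure, the smaller p-value at 0.025 and, if that is significant, the other at 0.05. Add the same two comparisons to the Statistical analysis section beside the within-group paired tests; if the full protocol already names them, only the Holm wording is new.

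State openly that any comparison of adverse events, or of 24 with 300 cGy, lies outside this 5%. Whether those are tested, estimated or described is for the sponsor to decide.

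The cost is a few sentences, with no change to patients, visits or treatment. There is one small downside. If 97.5% intervals are reported alongside, the interval for the second comparison can include zero although Holm rejects it, namely when its p-value lies between 0.025 and 0.05. The plan should say in advance that the Holm result decides.

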### Statistical analysis

Baseline characteristics according to the three groups will be compared using Student’s unpaired *T*-test or Wilcoxon’s rank sum test for continuous values. For categorical variables, the chi-squared test or Fisher’s exact test will be performed. A paired *t*-test or Wilcoxon’s signed test will be performed to evaluate the changes after 6 months from baseline in each group.

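### The only analysis stated for the 6-month ADAS-K change uses baseline only by subtraction and leaves out the randomisation strata; name a baseline- and strata-adjusted comparison of each dose with sham

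*Protocol article*

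**What the plan says.** In the Protocol article, Outcome measures sets the efficacy endpoint: "The primary endpoint is the score change of ADAS-K" at 6 months. Table 2 schedules ADAS-K at V1, V10 and V11, so every randomised patient should have a baseline score.

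Baseline and randomization (Visit 2) allocates patients to the three arms "by stratified block randomization using a random number table". The stratification factors are not named.

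Statistical analysis assigns the unpaired t, rank-sum, chi-squared and Fisher tests to baseline characteristics. For the 6-month change it names a paired t-test or a Wilcoxon "signed test will be performed to evaluate the changes after 6 months from baseline in each group". No covariate is mentioned, and no test of the change between arms is named.

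Outcome measures also says that "the primary endpoint evaluation will be analyzed by three institutions", with a further look at whether institutions differ.

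Sample size calculation calls the study exploratory and states "80% power and a 2-sided alpha of 0.05" with a Bonferroni correction. It adds that "it is difficult to calculate the appropriate effect size for the treatment and control groups". The Discussion gives the aim as comparing each dose with sham.

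**The concern.** The stated tests can use baseline ADAS-K in one way only, by subtracting it. That fixes its coefficient at 1. When the baseline-to-6-month correlation is below 1 and the two SDs are similar, the best coefficient is smaller, so the change score carries avoidable noise. Part of any chance difference between arms at baseline then also passes into the difference in change.

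The strata that shaped the allocation are also unused. If they predict outcome, their variance stays in the error term.

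A more basic gap is that no stated test compares either dose with sham. The two points are separable. A sponsor could close that gap with an unpaired t-test on change and still have an unadjusted analysis. In a trial of 60 patients, whose main product will be effect estimates, precision that can be had from data already collected is worth taking.

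**Working it through.** **Inputs.** From Sample size calculation: 20 per arm, 80% power, overall two-sided alpha 0.05, Bonferroni. Assumed: two comparisons (each dose against sham), hence 0.025 each; a correlation ρ of 0.5 to 0.9 between baseline and 6-month ADAS-K; and a ratio k of the 6-month SD to the baseline SD, first 1, then 1.2. The article gives no ρ, SD, effect size or dropout rate.

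**The plan's own figure.** Without an effect size, SD or dropout rate, 20 per group can be neither reproduced nor refuted. Solved backwards at 80% power and two-sided 0.025, it corresponds to a standardised difference in change of (2.241 + 0.842) × √(2/20) = 0.975 by normal approximation, or 1.009 by noncentral t.

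**Variance ratio.** The variance of the ANCOVA estimate relative to that of raw change is

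f = k²(1 − ρ²) / (1 + k² − 2ρk),

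which is (1 + ρ)/2 when k = 1.

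**Power.** Start from 80% on a raw-change comparison of one dose with sham. That comparison is hypothetical, because the article does not name one. By normal approximation, power = Φ(3.083/√f − 2.241). For ρ = 0.5: 3.083/0.866 − 2.241 = 1.319, giving 90.6%.

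The normal figures ignore the small-sample cost. With q covariates in a two-arm fit of 40 patients, the residual degrees of freedom fall from 38 to 38 − q, and chance covariate imbalance multiplies the variance by about 1 + q/(37 − q). That factor is 1.028 for baseline alone, and 1.088 for baseline plus two strata terms of no prognostic value.

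| ρ | f (k = 1) | Normal approx. | t, baseline only | t, baseline + two null terms |
|---|---|---|---|---|
| 0.5 | 0.75 | 90.6% | 89.7% | 87.7% |
| 0.6 | 0.80 | 88.6% | 87.6% | 85.4% |
| 0.7 | 0.85 | 86.5% | 85.4% | 83.0% |
| 0.8 | 0.90 | 84.3% | 83.2% | 80.6% |
| 0.9 | 0.95 | 82.2% | 80.9% | 78.3% |

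The gain from baseline alone is therefore about 10 points at ρ = 0.5, falling to about 1 at 0.9. The last column is a pessimistic case: two arms only, useless strata, and no credit for the balance that stratified allocation gives. Fitting all 60 patients in one three-arm model spreads the cost, and the gain with two null terms is then about 9, 4, 2 and 0 points at ρ = 0.5, 0.7, 0.8 and 0.9.

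**Unequal SDs.** With k = 1.2, f is 1.08/1.24 = 0.871 at ρ = 0.5, 0.7344/0.76 = 0.966 at 0.7, and 0.5184/0.52 = 0.997 at 0.8. The normal-approximation gains shrink to 5.6, 1.5 and 0.1 points.

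**Dropout.** With 16 evaluable per arm, the t figures for baseline only are 89.4%, 85.1%, 82.8% and 80.6% at ρ = 0.5, 0.7, 0.8 and 0.9. The gains hardly change.

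**Baseline imbalance.** With 20 per arm, the difference in baseline means has a standard error of √(2/20) = 0.316 baseline SD. Given an imbalance of that size and k = 1, the expected difference in raw change shifts by (1 − ρ) × 0.316. At ρ = 0.7 that is 0.095 baseline SD. The SD of change is √(2 × 0.3) = 0.775 baseline SD, so the shift is about 0.12 SD of change. ANCOVA removes it.

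**The case against.** The strongest objection is that this is a condensed article. Covariates are commonly left to a full protocol or analysis plan, neither of which is shown, and defining the endpoint as a change does not exclude adjustment, since ANCOVA of change has the same endpoint. This stands to a point: nobody can say from the article that the final analysis will be unadjusted. But the article is not silent. It names the method for the 6-month change, and that method cannot adjust.

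It is also fair that no raw-change comparison with sham is stated, so there is no fixed test that loses power. A reader might infer a definite loss of 4 to 10 points in this trial. The documents do not support that figure. It needs ρ between 0.5 and 0.8, equal SDs, 80% starting power and a test the article never names.

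Three further inferences go too far:

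- **Bias.** Under randomisation, a difference in raw change is unbiased. The shift shown above is conditional on an observed imbalance.
- **Strata.** Leaving them out widens the intervals only if they are prognostic. They are unnamed, so no benefit can be computed, and weak terms can cost a little power.
- **Institutions.** The by-institution analysis is described as additional. Nothing says it replaces a model term or is meant to answer the primary question, and enrolment per site is not given. A power figure for a single institution would test a purpose the article does not state.

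Finally, the study calls itself exploratory. That lowers the stakes for a formal test, but not the value of precise estimates.

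**Conclusion.** The point holds as a poorly chosen stated method with an inexpensive improvement. It is not a demonstrated loss of a fixed size. The one analysis named for the 6-month ADAS-K change ignores the randomisation strata and uses baseline only by subtraction, and a later unadjusted comparison with sham would inherit both features.

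Against 80% power on raw change (20 per arm, two-sided 0.025), the gain from adjustment is about 0 to 10 points over correlations of 0.9 down to 0.5. It is smaller if the 6-month SD exceeds the baseline SD, and at high correlation with uninformative strata it may vanish or turn slightly negative. The range rests on assumed correlations and SDs and on a Bonferroni split over two comparisons. Whether an unseen analysis plan already adjusts cannot be judged. The change is worth making, but it ranks below naming a between-arm test at all.

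**What to change.** In Statistical analysis, name the primary efficacy analysis as one ANCOVA of 6-month ADAS-K change on treatment arm (three levels), baseline ADAS-K as a continuous covariate, and the stratification factor or factors actually used in the randomisation table. Report each dose-versus-sham adjusted difference with its confidence interval, applying the Bonferroni correction already planned. Use the same model for 12-month ADAS-K, the other scales and the SUVR changes, each with its own baseline value. The within-group tests and the by-institution analysis may stay as descriptive additions.

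The cost is wording and a few degrees of freedom. Baseline scores and strata are already recorded for every randomised patient. Fixing the covariates before data are seen also removes a later choice among models. If power is quoted for the revised analysis, show it over a range of assumed correlations and SD ratios.

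### The only test named for the 6-month change is a paired test within each arm, which does not deliver the comparison with sham that the article promises

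*Protocol article*

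**What the plan says.** All references are to the protocol article.

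- **Outcome measures:** "The primary endpoint is the score change of ADAS-K (range 0–70, higher scores indicate a worse outcome) 6 months after baseline", together with the number of adverse events. A response is also judged against the patient's own starting score: "The amount of change will be evaluated as a valid response if it shows an improvement of≥5% from the baseline score".
- **Statistical analysis:** the two-sample tests for continuous data are introduced with "Baseline characteristics according to the three groups will be compared using". A sentence on categorical variables follows and names no outcome. The last sentence covers the 6-month change: a paired t-test or Wilcoxon "signed test will be performed to evaluate the changes after 6 months from baseline in each group". The section names no other test of that change.
- **Sample size calculation:** the study is described as an exploratory pilot whose purpose is to compare efficacy. It has a comparative three-arm parallel design, Bonferroni correction, 80% power and two-sided alpha 0.05, with 20 patients per group after allowing for dropout.
- **Discussion:** the reason for the control arm is explicit: "To rule out a placebo effect, the control group will receive sham irradiation". The two doses are used "to verify the treatment effect compared with that in the control group (sham RT)".
- **Baseline and randomization (Visit 2):** allocation is 1:1:1 by "stratified block randomization using a random number table". The stratification factors are not named.

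**The concern.** The question posed is comparative, but the test stated for the 6-month change is not. A paired test in an LDRT arm asks whether that arm's mean ADAS-K change differs from zero. In a sham-controlled Alzheimer's trial, zero is not the right reference. Untreated patients tend to worsen, while practice on the test, expectation and regression to the mean can move scores the other way. The sham arm exists to carry all of these so that they cancel in the difference between arms. A test run in each group separately never takes that difference.

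The error can go in both directions. If all arms improve alike, an LDRT arm can look effective when it is not. If LDRT only prevents decline, its arm shows no change and can look ineffective when it works. The second case matters here, because the Discussion itself says that existing drugs merely slow deterioration.

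**Working it through.** **Step 1. The plan's own figure.** The 20 per group can be neither reproduced nor refuted, because no effect size, SD or dropout rate is given. Solved backwards for 80% power with 20 analysed per group (normal approximation), it corresponds to:

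- between two arms: a difference of 0.89 SD at alpha 0.05, or 0.98 SD at 0.025;
- within one arm, paired: a mean change of 0.63 SD of change at 0.05, or 0.69 at 0.025.

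So the stated size does not reveal which test it was meant for.

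**Step 2. Stated aim against stated test.**

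| Place | What it commits to | Reference |
|---|---|---|
| Sample size calculation | comparing efficacy across three arms, Bonferroni | other arms |
| Discussion | excluding a placebo effect, verifying each dose | sham |
| Outcome measures | response of at least 5% | own baseline |
| Statistical analysis | paired test of the 6-month change | own baseline |

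No section names a test or estimate of the ADAS-K change for either dose against sham. The one further analysis of the primary endpoint in Outcome measures looks for differences among institutions, not arms.

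**Step 3. Common improvement, no treatment effect.** Assumptions, none of them given in the article: 20 analysed per arm, mean improvement of 2 points in every arm, SD of change 4, 5 or 6.

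The paired t-test has noncentrality (2/SD) × √20 on 19 degrees of freedom. Call its rejection probability p. The arms are independent, so the chance that at least one LDRT arm is significant while sham is not is (1 − p) × [1 − (1 − p)²].

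| SD | Noncentrality | p at 0.05 | LDRT significant, sham not | p at 0.025 | LDRT significant, sham not |
|---|---|---|---|---|---|
| 4 | 2.24 | 0.56 | 35% | 0.44 | 38% |
| 5 | 1.79 | 0.40 | 38% | 0.28 | 35% |
| 6 | 1.49 | 0.29 | 35% | 0.20 | 29% |

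Example at SD 5 and alpha 0.05: 0.603 × (1 − 0.603²) = 0.603 × 0.636 = 0.38. Applying Bonferroni to the paired tests therefore does not cure the problem: the range is 29 to 38% at 0.025 against 35 to 38% at 0.05.

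**Step 4. LDRT halts decline.** The mean change in the LDRT arm is then zero. The noncentrality is zero, and the paired test rejects with probability 5% (2.5% in the direction of improvement), however far sham has fallen. If sham worsens by 0.8 SD, for example, a t-test against sham at 0.025 with 20 per arm has about 58% power, while the paired test finds improvement in 2.5% of trials.

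**Step 5. What the between-arm test can do.** For a 2-point difference with 20 per arm, the unadjusted t-test has noncentrality (2/SD) × √10 on 38 degrees of freedom. At two-sided 0.025 its power is 24%, 15% and 11% for SD 4, 5 and 6.

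**The case against.** **The comparison with sham is intended.** A reader might infer that the randomised control goes unused, or that the trial cannot compare the two doses. The document does not support either. The comparison is announced in Sample size calculation and in the Discussion, Bonferroni correction presupposes several comparisons, and the randomised data would allow every contrast. What is lacking is a named test that delivers them. This objection stands, and it limits the point to a mismatch between promise and stated test.

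**The analysis plan may hold the between-arm test.** A short article may leave detail to a plan that is not shown, and the section does not call the paired test primary or sole. But the article is not silent on the 6-month change: it names a test, and that test does not fit the question. A between-arm analysis elsewhere would still have to be reconciled with this sentence.

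**The categorical tests might compare responders across arms.** The sentence on them is not expressly limited to baseline, and a 5% response is defined. This reading is possible but less natural, since the sentence continues from baseline characteristics and mentions no outcome. It would not cover the ADAS-K change score in any case.

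**The figures are illustrative.** The SD, the common 2-point shift and the reading of significance in LDRT but not in sham are assumptions; the article states no such decision rule. That is correct. The mismatch rests on the text, and the figures show only how far it could mislead.

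**The study is an exploratory pilot.** That softens the consequences. It does not make a within-arm change an estimate of treatment effect, and the closing paragraph of the Discussion still expects the trial to provide evidence on efficacy.

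**Conclusion.** The point holds in this form: the only test the article names for its 6-month efficacy change works within arms and does not deliver the comparison with sham that the same article promises. This follows from the text and needs no figure.

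Its possible size depends on the assumptions of 20 per arm, a 2-point improvement common to all arms and an SD of change of 4 to 6. With no treatment effect, each paired test at 0.05 is then significant with probability 0.29 to 0.56, and a pattern that favours at least one dose over sham appears in about 35 to 38% of trials. In the opposite case, complete halting of decline goes undetected except at the alpha level. Because this touches the primary efficacy conclusion and costs little to correct, it should be corrected before unblinding; a later switch from the published test could look data-driven.

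**What to change.** Replace the sentence on the 6-month change by a statement along these lines:

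- The primary efficacy analysis is the between-arm difference in 6-month ADAS-K change, 24 cGy against sham and 300 cGy against sham, each tested at two-sided 0.025 (Bonferroni).
- The model is an ANCOVA with arm, baseline ADAS-K and the actual randomisation stratification factors. The article does not name these factors, so the sponsor should confirm them.
- The contrast of 24 cGy with 300 cGy is secondary. Within-arm changes are descriptive.

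ANCOVA is a reasonable choice rather than the only valid one; the essential change is that the primary test compares arms.

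**Cost:** wording in the protocol and analysis plan, with no new data or patients. **Downside:** the between-arm test has low power for modest effects, about 11 to 24% unadjusted for a 2-point difference at SD 6 to 4. The change makes the conclusion valid but not well powered, so the report should lead with estimates and confidence intervals and should not read a non-significant result as absence of effect.
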